#### Randomization method

Randomization will be performed after obtaining informed consents. A secure online computerized randomization system will be utilized for randomization to ensure allocation concealment. This centralized web-based platform incorporates multiple functional modules for randomization, data entry, and management, and will be overseen by an independent statistical team. Qualified participants will be assigned to the acupuncyure or placebo acupuncyure groups in a 1:1 allocation ratio, employing stratified block randomization by age (< 35 years vs. ≥ 35 years) through a computer-generated system. Upon enrollment of eligible subjects, personnel responsible for randomization will log into the central randomization system via the internet to obtain a randomization number.

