#### Secondary outcomes

The secondary outcomes include the number of follicles ≥ 14 mm, E2 level, and endometrial thickness on the hCG trigger day; the number of retrieved oocytes, metaphase II (MII) oocytes, and two pronuclei (2PN) fertilizations; as well as the rates of 2PN fertilization, available embryos, high-quality embryos, implantation, cycle cancellation, biochemical pregnancy, pregnancy loss, sustained pregnancy, and live birth. The outcomes of IVF-ET and their definitions are summarized in **Table 4**. While the post-treatment observation will be terminated at about 24 weeks, data on live birth will be obtained through the participating centers’ mandatory, complete follow-up system extending to the end of pregnancy.

**Table 4 T4:** Diagnosis definitions of IVF-ET outcomes.

Diagnosis	Definition
Primary outcomes	
clinical pregnancy rate (CPR)	the number of clinical pregnancies divided by the total number of embryo transfer cycles.
Secondary outcomes	
Outcomes of IVF-ET	
2PN fertilization rate	the number of 2PN embryos divided by the number of MII oocytes
available embryo rate	the number of transferable embryos divided by the number of 2PN fertilization
high-quality embryo rate	the number of high-quality embryos divided by the number of normally fertilized cleavage embryos. High-quality embryos were defined based on the day of embryo transfer, according to the Istanbul consensus and Gardner criteria, as follows: Day 2: embryos with 4 cells, <10% fragmentation, and absence of multi-nucleation; Day 3: embryos with 8 cells, <10% fragmentation, and no multi-nucleation; Day 5: blastocysts at stage 4, with inner cell mass and trophectoderm both graded as A (17, 18).
Implantation rate	the number of gestational sacs divided by the number of embryos transferred.
cycle cancellation rate	the number of cancelled embryo transfer cycles divided by the number of embryo transfer cycles
biochemical pregnancy rate	the number of patients with positive serum b-hCG pregnancy test results divided by total embryo transfer cycles
pregnancy loss rate	the number of pregnancy termination cycles within 12 weeks divided by the number of embryo transfer cycles
sustained pregnancy rate	the number of cycles of pregnancy greater than 12 weeks divided by the number of embryo transfer cycles
live birth rate	the number of live births divided by total embryo transfer cycles.
Scale measurement	

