self-rating anxiety scale (SAS)	SAS consists of 20 items, and its measurement is determined by calculating the sum of the scores of each item

Additionally, ovarian reserve will be assessed using AFC and serum levels of AMH, FSH, LH, and E2. AFC and serum levels of FSH, LH, and E2 will be measured on days 2 to 5 of the menstrual cycle, while AMH can be measured on any day of the menstrual cycle. These assessments will be conducted both before and after the acupuncture intervention, with the post-intervention assessment scheduled during the menstrual period of the IVF cycle.

Anxiety levels will be evaluated using the Self-Rating Anxiety Scale (SAS). The total SAS score reflects the severity of anxiety symptoms, with a standard cutoff score of 50 used to classify participants into four categories: no anxiety (<50), mild anxiety (50–59), moderate anxiety (60–69), and severe anxiety (≥70) (19). The SAS will be performed before the first acupuncture session and within 24 hours after the final session.

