#### Statistical analysis

Analyses will be performed using SAS version 9.3 (SAS Institute Inc., Cary, NC, USA). The intention-to-treat (ITT) principle will be applied to all data analyses in this study. Multiple imputation will be employed to manage missing data. Continuous variables will be reported as mean ± standard deviation or median (interquartile range), and categorical variables as frequencies (percentages).

The primary outcome, CPR, was analyzed using multivariate logistic regression to calculate adjusted odds ratios (aORs) with 95% confidence intervals (CIs). The dependent variable in the model was clinical pregnancy (yes/no), and the independent variable was group allocation. The selection of covariates for adjustment was based on their established clinical relevance to IVF outcomes and any observed baseline imbalances between groups (p < 0.10). These covariates may include centers, age, baseline FSH level, AFC, COH protocol, number of retrieved oocytes, type of ET, number of embryos transferred, etc. Model fit was assessed using the Hosmer-Lemeshow test, and multicollinearity was evaluated via variance inflation factors. Additionally, a Per-Protocol (PP) analysis for priamry outcome will be performed as a sensitivity analysis. Other between-group comparisons will be performed using independent t-tests/Wilcoxon rank-sum tests for continuous data and chi-square/Fisher’s exact tests for categorical data, as appropriate. A two-sided *p* < 0.05 will define statistical significance.

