## Discussion

This trial is designed to evaluate the efficacy and safety of acupuncture in improving the CPR and ovarian function in women with DOR undergoing IVF-ET.

DOR manifests as a reduction in the number of oocytes and compromised oocyte quality, a reduction in CPR and LBR, and an increase in miscarriage rates (23). In individuals with DOR, the CPR and LBR persist at a low level, regardless of age (4, 23, 24). In the context of ovarian reserve assessment, the primary concern for patients is their ability to achieve pregnancy and ultimately deliver a live birth. Given the extended observation period necessary to evaluate the LBR, we selected the CPR as the primary outcome measure.

Additionally, ovarian reserve testing-related indicators, including AFC and serum levels of AMH, FSH, LH, and E2, will be selected as secondary outcome measures. Ovarian reserve testing provides valuable information for assessing ovarian reserve and reproductive potential, as these factors serve as key determinants of pregnancy outcomes (4). Ovarian reserve is typically evaluated using several indicators, including age, AFC, and levels of FSH and AMH (1). Since pituitary FSH secretion is inhibited by feedback from ovarian factors, the resultant basal FSH level can serve as an indirect gauge of ovarian reserve (25). A rise in FSH levels during the early follicular phase is interpreted clinically as evidence of compromised ovarian hormone production, which is associated with a reduced ovarian follicular pool consistent with DOR (25). However, this test exhibits significant intercycle and intracycle variability, thereby limiting its reliability (26). AMH serves as a direct biomarker for the primordial follicle pool, as it is secreted from the granulosa cells of small, developing follicles. Therefore, serum AMH is considered the preferred biomarker for assessing ovarian reserve,although the absence of an international standard hinders direct comparisons across different assays (27). Serum AMH levels have demonstrated predictive value for clinical pregnancy in IVF-ET cycles among women with a diminished ovarian response (28). The AFC is defined as the total number of antral follicles with a diameter ranging from 2 to 10 mm, observed on ovarian ultrasound during the early follicular phase (1, 29). AFC measurements exhibit good inter-cycle and inter-observer reliability in centers with experienced sonographers (1, 29).

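### The IVF-cycle count outcomes are compared without the randomisation age stratum or baseline AFC, which gives up a modest amount of power that could be had at no cost

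*Protocol article*

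**What the plan says.** Under Randomization method, the protocol allocates women "in a 1:1 allocation ratio", "employing stratified block randomization by age (< 35 years vs. ≥ 35 years"). Table 1 schedules AFC at Visit 1, and Inclusion criteria requires AFC < 5, so every randomised woman has a pre-treatment value. Of the ovarian reserve measures, Secondary outcomes says: "These assessments will be conducted both before and after the acupuncture intervention".

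Statistical analysis gives CPR a logistic model with covariates: "These covariates may include centers, age, baseline FSH level, AFC, COH protocol", among others. It then assigns all remaining comparisons: "Other between-group comparisons will be performed using independent t-tests/Wilcoxon rank-sum tests for continuous data", and chi-square or Fisher's "exact tests for categorical data, as appropriate". The outcomes under that rule include follicles ≥ 14 mm and "the number of retrieved oocytes, metaphase II (MII) oocytes, and two pronuclei (2PN) fertilizations", as well as biochemical pregnancy, sustained pregnancy and live birth.

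The Discussion gives the protocol's own view of prognosis: "Ovarian reserve testing provides valuable information for assessing ovarian reserve and reproductive potential, as these factors serve as key determinants of pregnancy outcomes". It lists age and AFC among the indicators of ovarian reserve.

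**The concern.** The design balances the arms on age, and the protocol regards ovarian reserve as prognostic. The rule for the other outcomes uses neither fact. A two-sample test leaves the variation explained by age and AFC in the error term. When allocation was stratified on a prognostic factor, the test also uses a standard error that is too large for the design.

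The follicle and oocyte counts are where this matters most. They are the direct evidence on ovarian response, and the Discussion names ovarian function as a target of the trial alongside CPR. They arise only in the IVF cycle and have no baseline value of their own, so the stratum and baseline AFC are the natural covariates.

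**Working it through.** **Plan's own figure.** The protocol gives no effect size, SD or correlation for any secondary outcome, so there is nothing to reproduce on this point. Its only sample-size figure is for CPR: 38% vs 22%, two-sided 0.05, 80% power, 120 per group. Standard formulas give 125 (unpooled variance) to 128 (pooled), and power at 120 is 77.5%. The dropout step is right: 120/0.8 = 150. Nothing below depends on whether 120 is correct.

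**Counts: power.** Let rho be the multiple correlation of age stratum and baseline AFC with the outcome (an assumption). Adjustment multiplies the variance by 1 − rho². From an 80% unadjusted base:

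power = Φ((1.96 + 0.842)/√(1 − rho²) − 1.96)

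| rho | 1 − rho² | interval narrower by 1 − √(1 − rho²) | 120 per arm worth 120/(1 − rho²) | power |
|---|---|---|---|---|
| 0.1 | 0.99 | 0.5% | 121 | 80.4% |
| 0.2 | 0.96 | 2.0% | 125 | 81.6% |
| 0.3 | 0.91 | 4.6% | 132 | 83.6% |
| 0.4 | 0.84 | 8.3% | 143 | 86.4% |

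Simulation with age-stratified allocation of 240 women agrees. At a total R² of 0.07 (rho about 0.26), power was 80.1% unadjusted and 82.2% adjusted.

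**Counts: type I error.** If age alone explains a share R² of the variance, stratified allocation removes that share from the true variance of the difference, but the t-test does not credit it. Its actual level is about 2 × (1 − Φ(1.96/√(1 − R²))):

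- R² 0.02: 1.96/√0.98 = 1.980, level 4.8%
- R² 0.05: 1.96/√0.95 = 2.011, level 4.4%
- R² 0.10: 1.96/√0.90 = 2.066, level 3.9%

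The simulation (8,000 null trials) gave 4.4% at 0.05 and 3.6% at 0.10, against about 4.9% for the adjusted model. At 0.02 it showed no shortfall (5.2% unadjusted, 5.5% adjusted). The test is conservative only to the extent that age is prognostic.

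**Binary outcomes.** The protocol gives no rates for sustained pregnancy or live birth, so the CPR rates are borrowed: 120 per arm, two equal age strata, control 22%, treatment odds ratio (0.38/0.62)/(0.22/0.78) = 2.17. Power over 4,000 simulations:

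| age odds ratio (assumed) | pooled chi-square | age-stratified Mantel-Haenszel | gain, points |
|---|---|---|---|
| 1.5 | 78.5% | 78.9% | 0.4 |
| 2 | 75.6% | 76.5% | 0.9 |
| 3 | 73.9% | 75.7% | 1.8 |
| 4 | 70.3% | 73.4% | 3.1 |

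At an age odds ratio of 4, type I error was 3.8% pooled and 4.3% stratified, each with a Monte Carlo standard error of about 0.3 points. That difference is too small to argue from.

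**The case against.** The strongest reply is that this is a preference for efficiency and not a mistake. Unadjusted tests on randomised arms are valid, the sentence is a generic closing line, and a separate analysis plan is still to be finalised (Data management). Validity is granted. But the protocol does not leave the method open: it names four tests, none of which carries a covariate or stratum, and the latitude it allows is only a choice among them.

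The second reply is about size, and most of it stands. A reader might infer a large loss, for example 89.9% power after adjustment at rho 0.5. Nothing in the protocol supports such a correlation. AFC below 5 can take only the values 0 to 4, and age is confined to 20–39, so both covariates have a narrow range. A gain of 1 to 2 points fits everything the protocol says.

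Two further inferences should be resisted:

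- **Precision for the pregnancy outcomes.** Adjustment there shows up as a little power, not as a narrower interval on the log odds ratio. The Discussion also describes pregnancy and live birth rates in this population as low at any age, which lends no support to a strong age effect.
- **Comparability with CPR.** One might argue that adjusting live birth would put it on the same footing as the adjusted CPR odds ratio. It would not: the CPR model may also hold centre, FSH, stimulation protocol, oocyte number and transfer variables, and odds ratios conditional on different covariates are not directly comparable.

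**Conclusion.** The point holds as a minor, worthwhile improvement, chiefly for the four count outcomes. The stated tests introduce no bias and do not inflate type I error. They are mildly conservative if age is prognostic, and they lose some power: roughly 0.4 to 6.4 points from an 80% base for rho 0.1 to 0.4, with the lower end more plausible. These rho values are assumptions, not figures from the protocol.

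For biochemical pregnancy, sustained pregnancy and live birth, the case is that the analysis should follow the randomisation. The expected gain is about 0.4 to 3 points of power, resting on assumed age odds ratios of 1.5 to 4 and on borrowed CPR rates. The primary analysis is not affected.

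**What to change.** In Statistical analysis, replace the general rule for these outcomes with one named method per outcome type:

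- **Follicles ≥ 14 mm; retrieved, MII and 2PN oocytes:** a linear model with robust standard errors containing arm, randomisation age stratum (< 35 vs ≥ 35) and baseline AFC, reporting the adjusted mean difference with its 95% interval.
- **Biochemical pregnancy, sustained pregnancy and live birth:** a Mantel-Haenszel test stratified by the randomisation age stratum.
- **Supportive:** the unadjusted tests now listed.

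Name the covariates before the data review meeting at which the analysis plan is to be finalised, so that they cannot appear to have been chosen from the listings. The cost is a few lines of text and a few model statements. Age stratum and baseline AFC are already collected, so no data, visits or participants are added.

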#### Sample size

Based on previous research (21, 22), we estimated that the CPR of IVF-ET in DOR patients after acupuncture pretreatment would be 38%, compared to 22% following placebo acupuncture pretreatment. A sample size of 120 participants per group has been determined to ensure 80% statistical power, with a two-sided alpha of 0.05. An initial total of 300 participants (150 per group) will be enrolled to allow for an anticipated 20% dropout rate.

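### Six before-and-after secondary outcomes are assigned to two-sample tests with no baseline covariate; a baseline-adjusted model would be more precise using data already collected

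*Protocol article*

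**What the plan says.** The Secondary outcomes section states that "ovarian reserve will be assessed using AFC and serum levels of AMH, FSH, LH, and E2", and that "These assessments will be conducted both before and after the acupuncture intervention". For anxiety, "The SAS will be performed before the first acupuncture session and within 24 hours after the final session". Table 1 agrees: all six measures are scheduled at Visit 1 (screening) and Visit 4 (the ovarian stimulation cycle).

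The Statistical analysis section describes covariate adjustment only for clinical pregnancy, in a logistic model. Of that model it says: "These covariates may include centers, age, baseline FSH level, AFC, COH protocol", among others. For continuous outcomes it then names the method: "Other between-group comparisons will be performed using independent t-tests/Wilcoxon rank-sum tests for continuous data". It gives no baseline covariate for these outcomes and does not state whether the follow-up value or the change is tested. Under Randomization method, allocation is stratified by age (below 35 years, or 35 and over).

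**The concern.** When an outcome is measured before and after treatment, its own baseline value is usually the most useful covariate available. A two-sample test on follow-up values leaves it out. A test on changes uses it, but with a fixed coefficient of 1 and not one estimated from the data. Either way the interval is wider than it need be. The named tests also leave out the age stratum used in randomisation.

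The plan sits oddly with itself here: baseline FSH and AFC are candidate covariates when pregnancy is the outcome, but not when FSH and AFC are themselves the outcome. The Discussion gives the trial's aim as improving ovarian function as well as pregnancy, and cites ovarian reserve as a route to higher pregnancy rates. Precision on these measures therefore matters for interpretation, although they are secondary.

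**Working it through.** **The plan's own figures.** There is no power statement for these six outcomes. The only sample-size figure concerns clinical pregnancy: rates that "would be 38%, compared to 22% following placebo acupuncture pretreatment", with the statement "A sample size of 120 participants per group has been determined to ensure 80% statistical power, with a two-sided alpha of 0.05". The dropout step reproduces: 120/(1 − 0.20) = 150 per group. The 120 itself does not reproduce exactly (unpooled normal formula: 7.849 × (0.38×0.62 + 0.22×0.78)/0.16² = 124.8, so 125; pooled: 128). That is a separate matter and nothing below depends on it. I use 120 per group only as a working number of women with data.

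**Assumptions.** The baseline/follow-up correlation ρ is not given, so I show 0.3, 0.5 and 0.7. I take the SD to be equal at both times and ρ equal in both groups, and ignore the few degrees of freedom spent on covariates. The formulas are for the t-test; for the Wilcoxon test they are only a guide.

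**Formulas**, in units of the follow-up variance:
- t-test on follow-up values: 1
- t-test on change: 2(1 − ρ)
- analysis of covariance (ANCOVA): 1 − ρ²
- ANCOVA relative to change: (1 − ρ²)/[2(1 − ρ)] = (1 + ρ)/2

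| | ρ = 0.3 | ρ = 0.5 | ρ = 0.7 |
|---|---|---|---|
| ANCOVA variance, 1 − ρ² | 0.91 | 0.75 | 0.51 |
| Reduction against follow-up test | 9% | 25% | 49% |
| Change-score variance, 2(1 − ρ) | 1.40 | 1.00 | 0.60 |
| ANCOVA relative to change, (1 + ρ)/2 | 0.65 | 0.75 | 0.85 |
| Reduction against change test | 35% | 25% | 15% |

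**In numbers of women.** Against a follow-up test, 120 per group with ANCOVA is worth 120/(1 − ρ²) = 132, 160 and 235 per group. Against a change test it is worth 120/[(1 + ρ)/2] = 185, 160 and 141.

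**Detectable difference at 80% power, two-sided 0.05.** The follow-up test detects (1.960 + 0.842) × √(2/120) = 0.362 SD. Multiplying by √(1 − ρ²) gives 0.345, 0.313 and 0.258 SD for ANCOVA. Multiplying by √[2(1 − ρ)] gives 0.428, 0.362 and 0.280 SD for the change test.

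**Power at a true difference of 0.362 SD.** Follow-up test: 80% throughout. Change test: 65.8%, 80.0% and 95.1%. ANCOVA: 83.6%, 89.9% and 97.5%.

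ANCOVA is the most precise of the three at each ρ shown. Which unadjusted version is worse depends on ρ: the change test below 0.5, the follow-up test above it. The protocol does not say which is meant, so the size of the gain cannot be stated more narrowly.

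**The case against.** Four objections deserve an answer.

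*The text does not say that baseline is ignored.* A reader might infer that the planned tests run on post-treatment values alone, and take the 49% at ρ = 0.7 as the loss. The document does not support that. Measurement before and after treatment fits a two-sample test on changes equally well, and then the gain shrinks as ρ rises, to 15% at ρ = 0.7. This objection stands, which is why both comparisons are shown.

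*Nothing is invalid.* A reader might infer that chance baseline imbalance biases the result. It does not: under randomisation the unadjusted tests hold their type I error, and chance imbalance is already part of their standard error. This also stands. The expected cost is precision only.

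*The correlation is assumed and may be low.* Entry requires AFC below 5 and AMH below 1.2 ng/mL, and excludes basal FSH of 25 IU/L or more and anxiety scores above 70; restricting the baseline range tends to lower ρ. The Discussion calls FSH variable between and within cycles, though it describes AFC as reliable in experienced centres. By Table 1, screening may fall up to 8 weeks before the start and the repeat at about week 10, so the two values may be up to about 18 weeks apart. All this stands. At ρ = 0.3 the gain over a follow-up test is only 9%, though over a change test it is then 35%.

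*The analysis plan is not shown and is still to be finalised.* It may specify more. But the protocol does not leave the method open: it names the tests, so commenting on that choice is fair.

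**Conclusion.** The point holds as a gain in precision that needs no new data, not as an error. The protocol assigns six before-and-after outcomes to tests with no baseline covariate and leaves open which value is tested. At assumed correlations of 0.3 to 0.7, baseline adjustment would cut the variance by 9% to 49% against a test on follow-up values, or by 35% to 15% against a test on changes. At 0.5 the figure is 25% either way. These sizes rest on the assumed correlation and on equal SDs at the two times, and will differ between the six measures.

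Only secondary outcomes are affected. The primary analysis already has an adjusted model, and the sample size rests on clinical pregnancy alone.

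**What to change.** For AFC, AMH, FSH, LH, E2 and the Self-Rating Anxiety Scale, make the main analysis a linear model of the post-treatment value on group, the baseline value of the same measure and the age stratum (below 35, or 35 and over). Report the adjusted difference with its 95% confidence interval.

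Pre-specify a log scale for the hormones (AMH, FSH, LH, E2), with rank-based ANCOVA as the fallback for data that remain skewed and for AFC, which is a low count. Keep the t-test and Wilcoxon test for continuous outcomes with no baseline, such as the number of oocytes retrieved.

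The cost is wording in the protocol and analysis plan. No new measurement, visit or participant is needed. The Data management section has the analysis plan finalised at the data review meeting, so the change can still be made, and should be made before treatment groups are unblinded.

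### Four laboratory and implantation rates are defined over oocytes or embryos; a chi-square on the pooled counts, which Table 4 invites, would give p-values that are too small

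*Protocol article*

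**What the plan says.** The unit of randomisation is the woman. The Randomization method section assigns participants "in a 1:1 allocation ratio, employing stratified block randomization by age".

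Table 4, under Secondary outcomes, defines four rates whose units are nested within a woman:

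- Implantation is given as "the number of gestational sacs divided by the number of embryos transferred".
- For fertilization, the definition reads "the number of 2PN embryos divided by the number of MII oocytes".
- Embryo quality is expressed as "the number of high-quality embryos divided by the number of normally fertilized cleavage embryos".
- For available embryos, the table uses "the number of transferable embryos divided by the number of 2PN fertilization".

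The Statistical analysis section gives the primary outcome a logistic model. One general sentence then covers all other between-group comparisons. It prescribes a t-test or Wilcoxon test where the outcome is continuous, and otherwise "chi-square/Fisher’s exact tests for categorical data, as appropriate". It does not name the four rates. The article mentions no method for several units per woman.

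**The concern.** The listed tests all assume independent observations. Oocytes from one woman share her age, her ovaries, her partner and the laboratory. Two embryos transferred together also share one uterus. Positive correlation within a woman is therefore to be expected.

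The wording of Table 4 points towards pooling. The four rates are written in the same count-over-count form as the clinical pregnancy rate, which is an arm-level proportion. They also stand in one list with biochemical pregnancy and live birth, which are categorical. No per-woman proportion is mentioned. An analyst who takes Table 4 and the general test sentence literally would add up oocytes or embryos by arm and run a chi-square. Its standard error would be too small.

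The error bars on fertilization, embryo quality and implantation are at stake. The Discussion says the trial is to evaluate ovarian function as well as pregnancy, so these results would probably be used to explain any effect on pregnancy. Each would be judged at two-sided p < 0.05.

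**Working it through.** The plan gives no figure for these rates, so there is none to reproduce. The question is how far a pooled chi-square departs from 5%.

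**Inputs from the protocol article.** The planned evaluable number is 120 women per group (Sample size). Eligible women have AFC below 5, and one or two embryos are transferred (Inclusion criteria). The first suggests small clusters, and the second bounds the cluster size for implantation.

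**Assumptions, because the article does not give these values.** ICC 0.1 to 0.3; 1 to 6 MII oocytes per woman with mean 3.0; 2PN probability 0.75. For implantation, half the women receive one embryo and half two, at a rate of 20%.

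**Formulas.** With m units per woman, the design effect is DE = 1 + (Σm²/Σm − 1) × ICC. A pooled test at nominal 5% then has type I error 2 × [1 − Φ(1.96/√DE)].

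*Fertilization.* The size-weighted mean cluster is Σm²/Σm = 3.81, so DE = 1 + 2.81 × ICC.

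*Available-embryo rate.* The denominator is 2PN embryos, so clusters are smaller. With beta-binomial fertilization, the excess 2.81 is multiplied by 0.75 + 0.25 × ICC, that is by 0.775, 0.80 and 0.825. It becomes 2.18, 2.25 and 2.32.

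*Implantation.* Σm²/Σm = (0.5 × 1 + 0.5 × 4)/(0.5 × 1 + 0.5 × 2) = 2.5/1.5 = 1.67, so DE = 1 + 0.67 × ICC.

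| Rate | ICC 0.1 | ICC 0.2 | ICC 0.3 |
|---|---|---|---|
| Fertilization, DE | 1.28 | 1.56 | 1.84 |
| Fertilization, type I error | 8.3% | 11.7% | 14.9% |
| Available embryo, type I error | 7.6% | 10.4% | 13.2% |
| Implantation, DE | 1.07 | 1.13 | 1.20 |
| Implantation, type I error | 5.8% | 6.6% | 7.4% |

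**Simulation under the same assumptions** (beta-binomial, 120 women per arm, 20,000 runs per setting). The pooled chi-square rejects 8.3%, 11.8% and 14.8% for fertilization, and 5.8% to 7.5% for implantation. This agrees with the closed form.

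**Other cluster sizes** (120 women per arm, 3,000 runs). With a Poisson number of oocytes of mean 3 and probability 0.7, the pooled chi-square rejects 10.0%, 12.4% and 16.8% at ICC 0.1, 0.2 and 0.3, and 6.6% at ICC 0.05. The Monte Carlo standard error at 10% is √(0.1 × 0.9/3000) = 0.5 percentage points, so the decimals should not be leaned on. With mean 2 and probability 0.4, roughly the situation of the high-quality-embryo rate, it rejects 7.7%, 10.2% and 11.9%. With equal clusters the closed form runs from 6.2% (two units, ICC 0.1) to 18.6% (five units, ICC 0.3).

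**One proportion per woman.** In the 3,000-run simulations the t-test rejected 4.4% to 5.7% across all settings. Wilcoxon, run on 600 of the replicates, rejected 4.0% to 6.5%. Neither shows systematic inflation.

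**Efficiency.** For 80% against 70% fertilization at ICC 0.1, 0.2 and 0.3, the per-woman t-test has power 71%, 66% and 63%. A pooled comparison with a cluster-robust standard error has 79%, 70% and 64%. The loss is 8, 4 and 1 points.

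**The case against.** The best reply is that the article does not assign the chi-square to these rates. One general sentence lists two families of tests, to be used as appropriate, and a woman's own fertilization percentage is ordinary continuous data under it. A t-test or Wilcoxon on that percentage respects the unit of randomisation. This stands. A reader might infer that every listed test ignores the clustering and that the p-values will be too small whatever is done. The document does not support that, because one of the two listed routes holds its error rate.

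A reader might also infer that the per-woman test is unsuitable because it weights a woman with one oocyte like a woman with six. That is a matter of efficiency and estimand. Equal weight per randomised woman is a legitimate target. Pooling weights women by oocyte number, which is measured after randomisation and is itself a secondary outcome. The loss of power is also smallest at ICC 0.3, where the chi-square does most harm.

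It can further be said that such detail belongs in a statistical analysis plan, which is not shown. Silence alone would be no finding. Here, however, the article does state definitions and tests, and their most literal combination is an anticonservative test. The Data management section places finalisation of the analysis plan at the data review meeting, where efficacy endpoints and data listings are discussed. The unit of analysis is better settled before that.

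**Conclusion.** The point holds conditionally. If chi-square or Fisher is applied to pooled oocyte or embryo counts, type I error exceeds 5%: about 8% to 15% for fertilization, about 7.6% to 13% for the available-embryo rate, and about 6% to 7.5% for implantation. The direction needs only positive correlation within women. The size rests on assumed ICCs and oocyte numbers, none of which the article gives.

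A general statement that false positives become two to three times as likely would go too far. The ratio for fertilization is 8.3/5 = 1.7 at ICC 0.1, and reaches 2.3 to 3.0 only at ICC 0.2 to 0.3. For implantation it is 5.8/5 = 1.2 to 7.5/5 = 1.5.

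Only secondary outcomes are concerned. Clinical pregnancy after the first transfer is one yes/no result per woman and has no such clustering. The change is worth making before the analysis plan is final, but the main conclusion of the trial does not depend on it.

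**What to change.** Exclude the four rates from the chi-square/Fisher rule and state that the woman is the unit of analysis. The preferred method is a binomial GEE on events/trials with the woman as cluster, robust standard errors, and arm and age stratum in the model. Report the difference or ratio with a cluster-robust 95% confidence interval. In SAS, which the article already names, this is PROC GENMOD with a REPEATED statement for the woman. At minimum, prespecify one proportion per woman, compared by t-test or Wilcoxon. In either case say how women with a zero denominator are handled, for example those with no MII oocytes or no transfer.

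The cost is a sentence or two in the analysis section and a few lines of code. Confidence intervals will be wider than those of the naive chi-square, and the per-woman option may lose some power, as shown above. Sample size and conduct do not change.
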